## Abstract

**Background:**

Diabetic patients present with an accelerated atherosclerotic process and an increased risk for future cardiovascular events. In addition to the risk imposed by the disease itself, pharmacological treatment adds also a sizable risk, especially if certain classes of antidiabetic drugs are employed. Animal evidence indicates that dipeptidyl peptidase-4 inhibitors have anti-atherosclerotic effects, yet clinical data are scarcely available.

**Design:**

We plan to prospectively investigate the effects of dipeptidyl peptidase-4 inhibition with vildagliptin on a number of atherothrombotic markers and adipokines in patients with proven atherosclerosis and type 2 diabetes. The selected markers are: interleukin-6, high sensitivity C reactive protein, interleukin 1-beta, total adiponectin levels, matrix metallo-proteinase 9 and platelet reactivity testing. Sixty eligible patients will be randomized in a 2:1 ratio to vildagliptin/metformin or metformin only treatment, for a 3-month duration treatment. Blood sampling for the proposed investigations will be taken at enrollment and immediately after completion of the study period.

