### Rationale of dose, duration of treatment

Vildagliptin-metformin combination is approved by the ministries of health and is commercially available in Israel and Europe. It has been shown to induce significantly less hypoglycemic events and therefore lower sympathetic activation detrimental for cardiac patients. The effects of vildagliptin-metformin combination vs. metformin monotherapy will be assessed 3-months after initiation of therapy. The short duration of the study and frequent follow-up visits with weekly interaction with study personnel will ensure the safe conduct of this trial and improve participant adherence. The 3-month duration has been shown in previous marker centered studies to be sufficiently long to induce the anti-atherothrombotic and anti-atherosclerotic changes. Metformin has been chosen for the comparison group, for the following reasons: 1) the drug was shown to be one of the most efficacious therapeutic options available [23,24]; 2) the clinical experience with the drug is extensive; and 3) it is a component of the comparison group vildagliptin-metformin combination.

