### Baseline clinical evaluation

At baseline patients will undergo detailed assessment including: 1) focused medical history, past cardiovascular events and key clinical findings, 2) body mass index (BMI) measurements, 3) physical examination and medication history. Based on current medication patients will be initiate a wash-out period of 2-weeks as described below.

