### Prior antidiabetic medication washout

Eligible patients (Hb A1c ≥7% and ≤ 9%) who receive current anti-diabetic monotherapy (not including metformin or a DPP4i) who consent to participate in the study will initially receive substituted antidiabetic treatment with metformin. Prespecified substitution of oral antidiabetic monotherapy is permitted if clinically reasonable and safe. A washout period of two weeks will take place prior to randomization. During this period, treatment with open label metformin will be carried out with blood glucose monitored regularly. Initial dose will be 850 mg once daily, with a dose increase to a maximum of 850 mg TID stabilization to a target of fasting glucose ≤130 mg/dL. For patients eligible for the study who receive current treatment with metformin monotherapy, a dose increase will also be allowed to a maximum of 850 mg TID aiming for stabilization to a target of fasting glucose ≤130 mg/dL.

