### Stabilization of oral anti-diabetic therapy for eligible patients not on previous therapy

Eligible patients (HbA1C ≥7% and < 9%) not on current antidiabetic therapy who will consent to participate on the study will be initiated with open-label metformin monotherapy for a period of two weeks prior to randomization. During this period, treatment with metformin will be carried out with blood glucose monitored regularly. Initial dose will be 850 mg once daily, with a dose increase to a maximum of 850 mg TID until stabilization to a target of fasting glucose <130 mg/dL.

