### Randomization

Randomization will be carried out following a 2-week period of stabilization on metformin mono-therapy as described above. Patients will be randomized in a 2:1 ratio to open label treatment with vildagliptin-metformin therapy or metformin mono-therapy. This study will be non-blinded to patients and treating personnel. All laboratory tests, the major study endpoints, will be performed by professionals blinded to treatment allocation. An interim analysis will be performed after the recruiting 50% of proposed study participants.

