### Follow-up visits

All patients will be invited for monthly follow-up visits with study coordinators. During these visits we plan to monitor both clinical and adverse events, verify medication compliance and evaluate any hypoglycemic events. Trained medical personnel will verify the home monitoring glucose journal. Changes in weight and in drug regiment will be recorded. At the completion of 3-months blood will be drawn for laboratory testing as done at baseline. Blood samples will not contain identifying information and all tests are to be performed in a blinded fashion.

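### The biomarker baseline is placed at enrollment, apparently before the two-week metformin run-in, so change to 3 months mixes a run-in effect of unknown size and direction with the randomised effect

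*Protocol article*

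**What the plan says.** The only statement that dates the first biomarker sample is in the Abstract (Design): "Blood sampling for the proposed investigations will be taken at enrollment and immediately after completion of the study period".

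The body gives this order of events:

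- **Baseline clinical evaluation** comes first and leads into the run-in: "Based on current medication patients will be initiate a wash-out period of 2-weeks as described below". The items listed are history, BMI, examination and medication history. No blood draw is named.
- **Prior antidiabetic medication washout** covers patients on another monotherapy, who are switched to open-label metformin: "A washout period of two weeks will take place prior to randomization". For those already on metformin: "For patients eligible for the study who receive current treatment with metformin monotherapy, a dose increase will also be allowed".
- **Stabilization of oral anti-diabetic therapy** covers untreated patients, who "will be initiated with open-label metformin monotherapy for a period of two weeks prior to randomization".
- **Randomization**: "Randomization will be carried out following a 2-week period of stabilization on metformin mono-therapy as described above".
- **Follow-up visits**: "At the completion of 3-months blood will be drawn for laboratory testing as done at baseline".

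Statistical methods and power calculation defines improvement as a fall of more than 20% from baseline to 3 months, and requires it in at least three markers. Specific aims sets a fall of at least 20% in IL-6 as the primary aim. Rationale of dose, duration of treatment says that effects "will be assessed 3-months after initiation of therapy". No section mentions a biomarker sample at randomisation.

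**The concern.** The run-in brings every patient to a metformin background before allocation. A biomarker baseline taken before it gives up that benefit for the endpoint. The measured change then contains two parts: what happens when a prior drug is stopped or metformin is started or raised, and what happens under the assigned treatment. The first part differs by entry therapy (diet only, another drug, metformin).

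This matters because the endpoint counts within-patient falls against a fixed 20% threshold, and the sentence stating the primary aim names no comparator. A 20% fall in the combination arm could be read as an effect of the combination when part of it arose before randomisation. An effect of the combination could equally be masked if the run-in raised the marker.

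**Working it through.** **1. Where the first sample falls.** Setting the sections side by side gives enrollment sample and baseline evaluation, then two weeks of metformin substitution, start or titration, then randomisation, then 3 months of assigned treatment, then the final sample. The interval from first to last sample is therefore 3 months plus two weeks. This order is inferred, because enrollment is not defined relative to randomisation.

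**2. What the change contains.** On the log scale, let R be the true change over the run-in and T the true change after randomisation. Change from enrollment is R + T; change from randomisation is T. Measurement error enters twice in either case.

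- Mean difference between arms: R precedes allocation, so it has the same expectation in both arms and cancels.
- Variance: Var(R + T) = Var(T) + Var(R) + 2 Cov(R, T). The enrollment baseline is noisier unless run-in changes tend to reverse by 3 months. The article gives nothing from which to size Var(R).

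**3. The plan's own figure.** Inputs from Statistical methods and power calculation: 10% versus 50%, 2:1 allocation, two-sided 5%, 90% power. Pooled-variance formula without continuity correction:

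- Pooled rate = (0.10 + 2 × 0.50)/3 = 0.3667
- 1.960 × √(0.3667 × 0.6333 × 1.5) = 1.157
- 1.282 × √(0.10 × 0.90 + 0.50 × 0.50/2) = 0.594
- Control n = (1.157 + 0.594)²/0.40² = 19.2, rounded up to 20; total 20 + 40 = 60

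Power at 20 + 40 is Φ((0.40 − 1.960 × 0.1320)/0.1037) = 91.4%. The stated size reproduces.

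**4. A shared run-in shift and the test.** With no drug effect and the same response rate in both arms, the exact type I error of the uncorrected chi-square test at 20 + 40 is 4.0% (rate 10%), 4.7% (20%), 5.1% (30%) and 5.5% (50%). A shared shift does not create a false difference.

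**5. A shared run-in shift and power.** The shifts are assumptions, in both directions, with N = 60. On the latent scale, the combination rate is Φ(Φ⁻¹(0.50) + s), with s = Φ⁻¹(control rate) − Φ⁻¹(0.10).

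| Assumed control rate | Combination, latent shift | Power | Combination, additive shift | Power |
|---|---|---|---|---|
| 5% | 36% | 79.5% | 45% | 94.8% |
| 10% (plan) | 50% | 91.4% | 50% | 91.4% |
| 20% | 67% | 95.9% | 60% | 86.8% |
| 30% | 78% | 96.1% | 70% | 85.7% |

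**6. One marker, no randomised effect.** For a marker where a fall is the improvement, P(fall >20%) = Φ((ln 0.8 − ln m)/SD), where m is the run-in multiplier. The SD of log change is assumed to be 0.4 to 0.8.

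| Assumed run-in effect | P(fall >20%) |
|---|---|
| 10% rise (m = 1.1) | 21% to 35% |
| none (m = 1) | 29% to 39% |
| 10% fall (m = 0.9) | 38% to 44% |

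The run-in contributes only the difference from the middle row. The middle row itself comes from assumed variability and would remain after any change of baseline.

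**The case against.** **The timing may be a matter of wording.** The pre-run-in draw rests on one word in an abstract. The baseline evaluation lists no blood draw, the flow figure is not shown, and the article condenses a fuller protocol. Study purpose and power text fit a draw at randomisation: the same 60 patients are enrolled and randomised, and effects are assessed 3 months from the start of therapy. This stands as far as certainty goes. It does not remove the point: enrollment is the only sampling time stated, the baseline evaluation precedes the run-in, and if a randomisation sample was intended the abstract needs correcting.

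**The comparison is randomised.** Study purpose and the power section specify comparison with metformin, and a shared run-in cancels. This stands in full for the between-arm test.

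**Stronger readings that the article does not support.** A reader might infer that the run-in inflates response in both arms. The article gives neither size nor direction: stopping a prior drug could raise a marker, and a patient already on metformin whose dose is not changed may show little or no effect. A reader might also infer a collapse in power. That happens only if control response rises while the combination stays at 50% (62.2% power at a control rate of 20%, 30.5% at 30%), and a run-in common to both arms gives no reason to expect that.

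**Conclusion.** The point holds as a weakness of interpretation, precision and planning, with moderate confidence because the timing is inferred. On the best reading, the change-based endpoint opens before the run-in and includes an effect of unknown size and direction that varies with entry therapy. Within-arm falls, including the 20% IL-6 target, then cannot be attributed to randomised treatment, and the 50% and <10% planning rates rest partly on that unquantified effect.

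The validity of the between-arm test is not in question. Under the assumed shared shifts, power at N = 60 lies between 79.5% and 96.1%, against 91.4% as planned. It can therefore move either way, and only the unfavourable latent shift takes it well below 90%. These figures illustrate a range; they do not estimate what will happen.

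**What to change.** Define the biomarker baseline as a sample drawn at the randomisation visit, after the two-week stabilisation and before the first dose of assigned treatment. Measure 3-month change, and the >20% responder rule, from that sample. Align three places: the sampling sentence in the Abstract (Design), Baseline clinical evaluation, and the baseline reference in Follow-up visits. For patients already enrolled but not yet randomised, add a sample at randomisation.

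The cost is small. One biomarker draw moves by two weeks. HbA1c eligibility still needs blood at enrollment, so some patients may have one additional routine draw. The planning inputs do not change, so the sample size stays at 60 and nominal power at 91.4%. The change does not remove ordinary within-person variability, nor any metformin effect still developing after two weeks, but the latter would be common to both arms.

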**Discussion:**

Demonstrating antiatherothrombotic properties of dipeptidyl peptidase-4 inhibitors on proven markers is of substantial clinical significance. Coupled with their proven good safety profile these findings could translate into a significant clinical benefit.

## Background

Patients with ischemic heart disease and diabetes are at a particularly high risk for the recurrence of cardiovascular events. Conversely, certain classes of oral antidiabetic medications have been shown to cause hypoglycemia as well as adverse cardiovascular effects [1-3]. Diabetes induces complex vascular changes, promoting accelerated atherosclerosis and hypercoagulability, as can be assessed indirectly by a number of markers. Principal perturbations include endothelial dysfunction, increased inflammatory plaque infiltration, adhesion molecule over-expression and adverse effects of circulating fatty acids and advanced glycosylation end products.

Animal studies have suggested numerous beneficial antiatherosclerotic changes of dipeptidyl peptidase-4 inhibitors (DPP4i), well beyond the effects on blood glucose alone [4,5]. Additionally, antiremodeling effects are proposed [6]. However, this feature has not been established in a clinical setting. Concomitant treatment with a DPP4i and metformin may offer an attractive glycemic reduction modality with synergistic mechanism of action while exerting additional vascular protective benefits. Reduction of inflammatory marker levels is of great clinical importance and has been shown to correlate with reduction in significant clinical events. Therefore, in the present study we plan to focus on possible anti inflammatory and atherothrombotic protective effects of DPP4i in a clinical setting.

Key representative markers for the present study are chosen in order to correctly represent alterations in: inflammation (hs-CRP), risk of atherosclerotic plaque rupture and matrix turnover (MMP-9), and platelet reactivity (aggregability tests). These markers are further detailed:

### Interleukin 6 (IL-6)

This established inflammatory marker has been shown to be increased in individuals with coronary artery disease [7,8]. Furthermore, diabetes has been referred to as a chronic inflammatory state. Therefore, a reduction in inflammatory markers in this high-risk population is likely to correlate with a corresponding reduction in the risk for atherothrombotic events.

### High sensitivity C-reactive protein (hs-CRP)

Marker of inflammation with a strong correlation with cardiovascular events even in normolipemic population [9]. Reduction of hs-CRP has been demonstrated with vildagliptin-pioglitazone combination, but data from patients with cardiovascular disease and vildagliptin-metformin combination are lacking [10].

### Platelet reactivity testing

Platelets are hyper-reactive in diabetic patients, and this heightened activity is closely linked to vascular events [11,12]. Perturbations in both structure and function have been described [13,14]. Reduction in reactivity is a viable surrogate of reduced thrombogenic milieu [15]. However, currently there are no human data on the effects of DPP4i on platelet function. We hypothesize that a combined vildagliptin-metformin therapy will be associated with a greater reduction in platelet reactivity as compared with metformin monotherapy.

### Adiponectin

Hormone with regulatory metabolic function secreted from the adipose tissue. Reduced levels of adiponectin were shown to be associated with obesity, metabolic syndrome, and diabetes, and to promote the atherosclerotic process [16-18]. Higher levels have been found to be protective [18,19]. Reduction in adiponectin levels induced by fatty diet has recently been shown to be corrected by DPP4i in mice [4], yet the effect in diabetic humans is unknown.

### Matrix metallo-proteinases 9 (MMP-9)

The MMPs are a large family of zinc-dependent, extra-cellularly acting endo-peptidases. Substrates of MMPs are proteins of the extracellular matrix and adhesion proteins. Patients with coronary artery disease were recently shown to have increased levels of MMP-9 [20]. A higher MMP-9 level was also shown to correlate with coronary artery ectasia [21], and to predict increased mortality in patients with coronary artery disease [22]. Accordingly, we hypothesize that treatment with combined vildagliptin-metformin therapy will be associated with significantly greater reductions in MMP-9 levels as compared with metformin monotherapy.

The effect of DPP4i on the above-mentioned parameters has not been studied in humans. Accordingly, the demonstration of significant improvements in markers of atherothrombosis and inflammation in high-risk diabetic patients is of great clinical importance and novelty that may be employed for the reduction of major cardiovascular events in this population.

## Study design

### Study purpose

To demonstrate that combined vildagliptin-metformin therapy is associated with clinically significant reductions in biological markers of inflammation, pro-thrombogenicity, and atherosclerosis as compared to metformin monotherapy in a population of diabetic patients with coronary artery disease who undergo cardiac rehabilitation.

The prespecified established biological markers of inflammation, pro-thrombogenicity, and atherosclerosis will include: interleukin-6 (IL-6 – primary biological marker), hs-CRP, platelet reactivity testing, MMP-9, interleukin 1 beta (IL-1 beta) and adiponectin levels.

Findings from this analysis will demonstrate the pleiotropic effects of DPP4i in a clinical setting, in addition to its established antiglycemic effects.

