### Specific aims

 2.1. Primary Aim: Demonstration of a significant (≥ 20%) reduction in the serum levels of interleukin 6 (IL-6)

 2.2. Secondary Aims:

 Improvement in other markers of atherothrombosis and inflammation:

 High sensitivity C-reactive protein (hs-CRP),

 Platelet reactivity

 Adiponectin levels

 IL-1 beta

 Matrix metallo-proteinase 9 (MMP-9)

 Additional exploratory markers including: IL-1 alpha, IL-17, TNF-alpha, MCP-1, monocyte subsets by FACS 

 Safety from hypoglycemic events

 Reduction in glycosylated hemoglobin (Hb A1c)

 Weight reduction

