### Treatment

The entire study group will be actively treated orally with either metformin (control group) or metformin-vildagliptin combination (intervention group), once or twice daily. No placebo medication is used in this study. The study is open-labeled. Endpoints are mostly laboratory ones, so the un-blinded design will have a minimal effect on the validity of the obtained results.

Treatment will be initiated as follows: (1) in the control arm, metformin dose will be based on the treatment prescribed at the end of the 2 week pre-randomization period; and (2) in the investigational arm, metformin will be replaced with combined metformin-vildagliptin treatment with an initial dose of once daily. Titration to the three times a day is permitted in accordance to investigators clinical judgment in the control arm, while in the metformin-vildagliptin combination, maximal dose will be twice daily.

Study patients and other treating physicians will be asked not to alter antidiabetic medication unless there is justifiable clinical urgency. As statin have proven anti-inflammatory and diverse pleotropic properties, statin type and dose will be recommended to remain fixed during the 3-month study period, unless otherwise clinically indicated.

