### Medication titration

Study design permits, based on blood glucose measurements and additional lab test if deemed necessary, modification of the medication dose with the goal of fasting glucose ≤ 130 mg/dl. In the control arm up-titration will be carried out with metformin, and in the treatment arm up-titration will be carried out with vildagliptin-metformin combination. If control of blood glucose cannot be achieved after maximal drug titration and there are repeated (>3) measurements of FPG > 300 mg/dl after nutritional consultation and exercise, the study investigator is encouraged to add antidiabetic treatment according to medical judgment and national guidelines. Deviations from study protocol are to be recorded in detail on appropriate eCRF. With the exception of severe exacerbations in glucose homeostasis noted earlier, all effort is to be made to maintain a stable treatment plan in coordination with the family physician. Patient’s adherence to study medication will be evaluated by pill-count at the follow-up visits.

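### The stated conclusion that the findings will show pleiotropic effects goes beyond the design, which identifies only the total effect of adding vildagliptin to metformin

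*Protocol article*

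**What the plan says.** All references are to the protocol article.

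- **Promised conclusion.** Study purpose ends: "Findings from this analysis will demonstrate the pleiotropic effects of DPP4i in a clinical setting, in addition to its established antiglycemic effects".
- **Motive.** Background reports animal studies suggesting benefits of this drug class "well beyond the effects on blood glucose alone", and adds that this has not been established clinically.
- **Contrast.** Under Treatment, patients are "actively treated orally with either metformin (control group) or metformin-vildagliptin combination (intervention group"), and "No placebo medication is used in this study". One reason given for choosing metformin as control is that "it is a component of the comparison group vildagliptin-metformin combination" (Rationale of dose, duration of treatment).
- **Glucose management.** Both arms allow "modification of the medication dose with the goal of fasting glucose ≤ 130 mg/dl" (Medication titration). The means differ: "In the control arm up-titration will be carried out with metformin, and in the treatment arm up-titration will be carried out with vildagliptin-metformin combination". In either arm, a further antidiabetic drug is encouraged only after maximal titration and more than three fasting readings above 300 mg/dL.
- **Glycaemic outcome.** Specific aims lists "Reduction in glycosylated hemoglobin (Hb A1c") among the secondary aims.

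**The concern.** A pleiotropic effect, in the sense the Background gives the idea, is one beyond glucose lowering. To show it, a trial must either hold glycaemia equal between the arms or have some way to separate a marker change that runs through glucose from one that does not. Here every patient is on metformin at randomisation. One arm then gains a second agent whose antiglycaemic effect the protocol calls established, and the other gains none.

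The protocol also supplies the rival explanation. Background ties diabetes to accelerated atherosclerosis and hypercoagulability, the IL-6 section describes diabetes as a chronic inflammatory state, and the platelet section says platelets are over-reactive in diabetes.

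What is at stake is the interpretation. If IL-6 or another marker falls more in the vildagliptin arm, the sentence in Study purpose would have this reported as pleiotropy, although part of the difference could come from better glycaemic control.

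**Working it through.** **1. The plan's own figure.** Inputs from Statistical methods and power calculation: responders 50% against 10% (the plan says below 10%), allocation 2:1, power 90%, two-sided 5%. With the pooled-variance formula without continuity correction, the mean proportion is (0.10 + 2 × 0.50)/3 = 0.367, and

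n(control) = [1.96 × √(0.367 × 0.633 × 1.5) + 1.282 × √(0.09 + 0.25/2)]² / 0.40² = (1.157 + 0.594)² / 0.16 = 19.2, rounded up to 20.

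This gives 20 + 40 = 60, as stated, with power 91.4%. The sample size is for the total difference between the regimens. Nothing in it depends on the mechanism, so the point changes no number in the plan.

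**2. The promise against the design.**

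| Needed to claim an effect beyond glucose | What the article provides |
|---|---|
| Equal glucose lowering in both arms | A second glucose-lowering drug in one arm only |
| Equal glycaemia reached | A shared fasting goal; control up-titrates metformin only, already titratable to 850 mg three times daily in the run-in |
| Correction of a residual gap | A further drug only after more than three fasting readings above 300 mg/dL |
| No expected glycaemic effect | HbA1c reduction is a secondary aim |

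A shared goal is not shared attainment. Between 130 and 300 mg/dL, a patient at maximal titration can stay above the goal without meeting the stated trigger for another drug.

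**3. Can the glucose-mediated part be sized?** Not from the document. The following only shows how the answer moves with assumed inputs.

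*IL-6 scale.* If the arms differ by d HbA1c points and IL-6 is multiplied by s per point of reduction, glucose alone gives a difference of 1 − s^d.
- d = 0 or s = 1: 0%
- d = 0.5, s = 0.9: 5.1%
- d = 0.7, s = 0.8: 14.5%
- d = 1.0, s = 0.8: 20%

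*Significance with no direct drug effect.* Let the arms differ by D standard deviations in glycaemic change, and let that change correlate r with marker change. The mediated difference is m = r × D, its standard error is √(1/20 + 1/40) = 0.274, and the chance of significance is 1 − Φ(1.96 − m/0.274) + Φ(−1.96 − m/0.274).
- D = 0 or r = 0: 5%, the nominal level
- D = 0.5, r = 0.2: 6.5%
- D = 0.8, r = 0.3: 14%
- D = 0.8, r = 0.5: 31%
- D = 1.0, r = 0.5: 45%

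*Responder scale.* With 10% in control, an intervention rate of 20%, 30%, 40% or 50% produced wholly through glucose would be declared significant with probability 14%, 39%, 70% or 91%.

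The results run from no effect to a large one. The article gives none of d, s, D or r, so it does not say where in this range the trial lies.

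**The case against.** The strongest reply is that the trial's operative question is already the total effect. The opening sentence of Study purpose, the design rationale, the platelet and MMP-9 hypotheses and the sample size all compare one regimen with the other, and no endpoint or decision rule depends on glucose independence. The Background phrase about effects beyond glucose concerns animals. The purpose sentence speaks of effects in addition to the antiglycaemic one, which can be read as effects on other systems. The Discussion calls the protective effects hypothesised and allows that fewer sympathetic activations, which it links to hypoglycaemia, may explain part of them. All of this stands. It limits the point to one sentence, but that sentence still announces a demonstration that the comparison cannot give.

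A reader might infer more than the documents support:

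- *That a sizeable glycaemic gap is certain.* The arms share a fasting goal, and the HbA1c aim states no between-arm size. Under Treatment, control may be titrated to three times daily, whereas in the other arm the combination replaces metformin and is limited to twice daily. The size of any gap is therefore open. Nor does the article say how many patients enter on metformin; diet-only patients are eligible.
- *That a marker improvement is just what lower glucose would produce.* The article links the diabetic state to inflammation and platelet reactivity. It does not say that three months of lower glucose reduces these markers.
- *That no analysis will separate the two routes.* The full protocol and analysis plan are not shown, and an HbA1c-adjusted analysis may be there. Its absence from the article is not the finding. Such an analysis would condition on a variable measured after randomisation, so it would not justify a promise of demonstration either.

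**Conclusion.** The point holds as a matter of what may be concluded. Study purpose ascribes to the trial a property that its design does not have. Randomisation identifies the total effect of adding vildagliptin to metformin on the markers; it does not identify the share that is independent of glucose. This follows from the two regimens, the titration rules and the HbA1c aim, and needs no assumed number.

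The size of the glucose-mediated share is unknown. The illustrations rest entirely on assumed inputs, and zero is among the possible values. The upper IL-6 figure matches the 20% primary aim only because the inputs at that corner give 20%, so it should not be read as an estimate. The comparison of the regimens remains valid as a test of the total effect, and the sample size, endpoints and conduct are unaffected.

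**What to change.** Replace the last sentence of Study purpose with wording such as: *The trial will estimate the effect of adding vildagliptin to metformin on the markers, which may include effects through glucose lowering.*

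As an exploratory analysis on data already planned, report each marker difference unadjusted and adjusted for change in HbA1c, side by side. State two limits with it:

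- The adjusted estimate conditions on a post-randomisation variable. Factors that affect both HbA1c change and marker change can bias it in either direction.
- It is imprecise with 20 controls. Even unadjusted, the 95% half-width is about 1.96 × 0.274 = 0.54 standard deviations of marker change.

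For both reasons, do not make persistence after adjustment the rule for claiming pleiotropy. Confounding or imperfect measurement of glycaemia could make a difference persist wrongly, and low precision could make a real one disappear.

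The cost is one reworded sentence, one extra table and a more modest conclusion. No change of comparator, dose or treatment rule is asked for.
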